## Abstract

**Background:**

The cognitive benefits of early non-pharmacological approaches have been demonstrated in older adults with mild cognitive impairment (MCI). However, older adults living in nursing homes have more severe cognitive impairment problems and lower initiative and compliance to participate in complex interventions. Hence, it important to investigate more attractive and sustainable methods to prevent or delay cognitive decline. The present study adopts the self-determination theory (SDT) as a theoretical framework to innovatively develop an integrated art-based intervention for older adults with MCI in nursing homes in China and aims to evaluate its effects on cognitive function, mental health, and other health-related outcomes.

**Methods:**

The study is a nursing home-based, cluster randomised controlled trial (RCT) that targets older adults (aged ≥ 60 years) with MCI in Fuzhou City, China. All nursing homes in the area covered by Fuzhou City are invited to participate. Eligible nursing homes are randomised to one of two groups: intervention group (receive a 14-week, 27-session intervention) and waitlist control group (receive the usual care). The SDT-based integrated creative art (SDTICA) program reasonably adopts the SDT as a theoretical framework to innovatively develop an integrated art-based intervention for older adults with MCI in nursing homes. The primary (global cognitive function and psychological indicator) and secondary (daily activity function, social function, and specific domains of cognitive function) outcomes will be measured at baseline, after the intervention, and during follow-up.

**Discussion:**

This study aims to evaluate the effects of SDTICA program on neuropsychological outcomes in older adults with MCI and provide scientific evidence for art-based non-pharmacologic interventions in nursing homes, which may reduce dementia risk in older adults with MCI.

**Trial registration:**

The trial was prospectively registered at the Chinese Clinical Trials Registry with the registration number ChiCTR2200061681 on 30 June 2022.

**Supplementary Information:**

The online version contains supplementary material available at 10.1186/s12877-023-03896-0.

## Background

According to the 2018 World Alzheimer’s Disease Report [1], there are more than 50 million people with dementia worldwide, and the annual social and economic burden caused by dementia reaches US $1 trillion. Currently, there are more than 15 million older adults with dementia in China, accounting for 25% of the global total. The social and economic burden of dementia accounts for 1.47% of the gross domestic product, which is higher than the global average [2, 3]. Nevertheless, due to the irreversible course of dementia and the limitations of treatment, early diagnosis and early intervention have become the focus of dementia prevention and treatment. Hence, the early diagnosis and preventive intervention of mild cognitive impairment (MCI), a potential precursor disease of dementia, has increasingly attracted the attention of researchers. MCI is a transitional stage between normal aging and mild dementia [4]. The incidence of MCI in adults aged 60 years and above in China is 15.54%; further, approximately 10-20% of MCI cases transform into dementia every year, and the risk of dementia in people with MCI is 10 times that of healthy older adults [2, 5]. Therefore, promoting dementia prevention and MCI treatment and taking targeted intervention measures as soon as possible is expected to prevent or delay the occurrence and progression of dementia; dementia prevention has positive significance for promoting healthy aging.

Notably, institutionalisation can also negatively impact an individual’s global cognitive function. Due to the miniaturisation of family structure and the change of people’s concept of pension, China’s pension model has gradually changed from traditional family pension to institutional pension, and the number of older adults in nursing homes has gradually increased [6]. A 22-year follow-up study found that older adults in nursing homes showed greater cognitive decline than those who remained in the community [7]. The results of several studies suggest that the incidence of cognitive dysfunction in older adults in nursing homes in China is higher than the overall incidence in the country [6–8]. A possible reason of institutional cognitive decline may be a lack of cognitively stimulating activity, and studies have shown that people who are chronically exposed to cognitively stimulating environments maintain higher cognitive function with age [7, 9–11]. Although activities such as playing cards or watching television are common in nursing homes, several studies have shown that these leisure activities are not sufficient to maintain cognitive health [12–14]. Cognitive stimulation (CS) is a kind of non-pharmacological intervention, which refers to a series of non-specific cognitive intervention activities that stimulate thinking, attention, and memory in groups of people in a social environment; these activities include reality-oriented activities, art activities, and topic discussions to improve the patient’s cognitive or social function [15]. A Bayesian network meta-analysis of 13 randomised controlled trials (RCTs) suggested that CS may be the best intervention for improving cognitive function in patients with MCI [16]. Thus, it is urgent to pay close attention to the cognitive function of older adults with MCI in nursing homes, and to construct and implement preventive intervention programs cantered on CS, so as to delay cognitive decline, promote physical and mental health, and improve quality of life. However, the number of studies on older adults in nursing homes is limited, and there is a lack of intervention approaches suitable for older adults with MCI in nursing homes.

In recent years, the benefits of art-based CS for cognitive and emotional states of the older adults with cognitive impairment have been continuously verified [17]. Art therapy (AT) is defined as “a form of psychotherapy that uses art media as its primary mode of communication”, and is subdivided into categories such as visual arts, music, dance, drama, and literature [18]. This has been developed as an effective intervention strategy, as it provides older adults with a complex and rich environment by producing multisensory stimulation, challenging cognitive tasks, and increased social interaction [19]. A meta-analysis of 11 RCTs reported that AT can effectively stimulate and improve cognitive function and reduce depression in older adults by maximising the integration of socialization, work creation, and story sharing [20]; another meta-analysis also confirmed the positive effects of AT on cognitive function in older adults with MCI [17]. Considering the practical application of non-pharmacological interventions in older adults with MCI in nursing homes, AT may be a more culturally and contextually appropriate option. This is because the older adults with MCI in nursing homes generally have the characteristics of advanced age, poor mobility, and limited social interaction [7, 21, 22], which increase the requirements on the content elements, intervention modes, and difficulty settings of interventions. In contrast, differences in individual educational backgrounds, interest tendencies, thinking habits, and receptive abilities also increase the challenge of applying cognitive interventions to promote brain health in this group of people. AT that relies on creativity and nonverbal expression may be a better option. First, AT focuses on the integration of personal and internal experience in the whole process of creation, rather than the analysis and judgment of works of art [23]. Hence, participants who accept AT do not need to have any experience or background in artistic creation, and thus it has good applicability and acceptability for older adults with MCI in nursing homes. Second, AT provides older adults with MCI in nursing homes with a communication channel for non-verbal communication, creating more opportunities for social and interpersonal interaction, enabling them to freely express their inner feelings in a supportive environment and relieving anxiety, depression, and social isolation, while gaining new skills and a sense of well-being [24–26]. Kim et al. found that group AT played a significant role in improving depressive state and self-expression in patients with MCI [25]. In addition, Pérez et al. reported that group music therapy can effectively improve the cognitive function and emotional state of older adults with cognitive impairment in nursing homes [26]. Nevertheless, there is no agreement on which type of AT provides the most benefit for treating dementia [27]. A meta-analysis found that different types of AT (including visual arts, music, drama, and poetry) showed significant improvements in at least one outcome measure such as cognitive function, behavioural symptoms, and emotional state [27]. This suggests that combining different types of integrated AT may potentially show more cognitive benefits than using a single type of AT [28]. But most of the studies on the application of AT to older adults with MCI in nursing homes have great heterogeneity in terms of research design, diagnostic criteria, and intervention modes moreover, these studies are mainly small-sample and single-centre studies, with few follow-up evaluations to determine the long-term efficacy of the intervention. Overall, research evidence is of low quality and the efficacy of the intervention is unclear [17]. Additionally, the lack of motivational theoretical guidance in the construction and implementation of most intervention programs often leads to insufficient motivation to participate in interventions and decreased compliance in the older adults with MCI, which has become the primary factor hindering the promotion of these intervention programs in the social environment [29, 30].

There is robust evidence that interventions guided by motivation theory can have a significant effect on the maintenance of individual behavioural changes [31, 32]. Further, self-determination theory (SDT) is a motivational theory commonly used in behavioural interventions [33]. It emphasises improving autonomy support, which is consistent with the autonomous supportive environment provided by AT [34]. Motivation, which is the initiating factor of individual activities and an important factor in maintaining the continuity of activities, is considered to be the most powerful and stable predictor of activity at the individual level [35]. Meeting the three basic psychological needs of autonomy, competence, and relatedness, and then promoting the generation of internal motivation and the internalisation of external motivation is important for the promotion and maintenance of positive behaviour change in older adults, thereby helping individuals maintain behavioural changes for up to 12 months [36–39].Therefore, this study attempts to apply SDT in the design and implementation of intervention programs for the older adults with MCI in nursing homes, in order to more effectively trigger and maintain participants’ positive behavioural changes.

To these ends, we can reasonably adopt the SDT as a theoretical framework to innovatively develop an integrated art-based intervention for older adults with MCI in nursing homes in China and conduct a methodologically rigorous RCT; moreover, a 6-month follow-up will be conducted to evaluate its short- and long-term effects on neuropsychological outcomes in older adults with MCI. We hypothesized that the 14-week, 27-session SDT-based integrated creative art (SDTICA) program could serve as a non-pharmaceutical intervention to effectively improve cognitive, psychological, and social functioning in older adults with MCI in nursing homes.

## Methods/Design

### Study design, setting, and ethics

The study is a cluster randomised, controlled, single-blind, parallel-group, multicentre trial conducted on older adults with MCI to assess the effects of the SDTICA program on cognitive function, mental health, and other health-related outcomes (Fig. 1). It will be conducted in nursing homes in Fuzhou City, China.

**Fig. 1 Fig1:**
[figure not shown]
Flow diagram of the study design

The nursing homes will be randomised on a 1:1 basis to the intervention (SDTICA program) or waitlist control (usual care) group. The waitlist control group will receive the usual care provided by the nursing home, and the intervention group will be exposed to the SDTICA program by professionally trained and qualified intervenors. The SDTICA program design will follow the Medical Research Council (MRC) guidelines on the evaluation and development of complex interventions [40]. A pilot trial will be conducted to assess the acceptability, safety, and feasibility of the SDTICA program. This study will be conducted, analysed, and reported in accordance with the Consolidation Standards of Reporting Trials (CONSORT) statement for cluster RCTs [40]. All procedures will be conducted in accordance with the Declaration of Helsinki. Ethics approval has been granted by the Ethics Committee of Fujian Provincial Hospital (K2022-05-015) and was registered in the Chinese Clinical Trials Registry with registration number ChiCTR2200061681 (trial registration data available at: http://www.chictr.org.cn/edit.aspx?pid=166566&htm=4).

### Nursing home recruitment and screening

All five-star nursing homes in Fuzhou City will be invited to participate in the study. Individuals recruited from nursing homes tend to have more advanced cognitive impairment compared with community-dwelling individuals [7]. The severity of cognitive impairment in study participants could impact their motivation and ability to participate in and adhere to a complex intervention [41, 42]. Hence, we will adopt multiple effective recruitment strategies. First, we will contact qualified nursing homes via telephone calls to explain the study. If a facility is interested in the study, we will visit the facility to provide more detailed information. Thereafter, prefeasibility assessment will be conducted to evaluate if nursing homes have resources to support recruitment and intervention, such as availability of social and care workers to assist in the study as well as a suitable venue for the SDTICA program. If the nursing home is eligible for selection and agrees to participate in the study, preselection screening will be conducted to identify eligible participants.

Nursing homes with the following criteria will be considered eligible:

Having a permit for the establishment of old-age care service institutions.Rated as five-star level according to the Pension Institutions Grade Division and Assessment [43]; the rating is performed by professionals who are qualified in terms of grade assessment and training. The level (one- to five-star level) is rated based on a comprehensive consideration of the environment, facilities and equipment, operation management, and service provision of pension institutions. The higher the level, the stronger the comprehensive ability of pension institutions in the abovementioned four aspects.Equipped with self-care area.Agree to participate in this study and are able to provide venue and personnel support.

Nursing homes with the following criteria will be excluded:

Participating, has recently participated, or plans to participate in another trial that conflicts with the SDTICA program or data collection during trial participation.Insufficient attention to this study, serious progress lag, and ineffective communication.The presence of certain difficulties in patient recruitment or organization to perform intervention activities, resulting in failure to promptly and accurately complete the study plan, and if these difficulties cannot be solved after communication efforts.

### Participant recruitment and screening

Participants will be nursing home-dwelling older adults with MCI (aged at least 60 years). Participant recruitment will be performed through public advertisements (e.g., posters, leaflets, and brochures), media outreach (e.g., local newspapers and website-published feature stories about the potential benefits of art-based intervention for cognitive function among older adults with MCI), mobilization meetings (to introduce potential participants to the symptoms and harms of MCI, as well as the content and benefits of the SDTICA program), art-based experience activities, and word-of-mouth by the residents and social workers who will be mobilized to invite participants for screening. Potential participants who respond to the recruitment strategies will be screened for study eligibility in a two-stage process.

#### Screening stage 1 (SS1)

The purpose and process of the study will be fully explained to each participant, and a written informed consent form will be signed by consenting participants. Neurophysiological assessment will be performed by qualified researchers to evaluate participants’ global cognitive function using a combination of the Montreal cognitive assessment (MoCA) and Mini-Mental State Examination (MMSE) [44, 45]. In addition, the activity of daily living (ADL) and functional activities questionnaire (FAQ) will be used to assess daily and social competency [46, 47]. Participants who meet all the following criteria will proceed to the second screening stage: (1) MoCA score ≤ 13/14 for illiterate individuals, ≤ 19/20 for individuals with 1 to 6 years of education, or ≤ 24/25 for individuals with 7 or more years of education [48]; and (2) MMSE score = 24–30 [49]. Cutoff MoCA scores will be used to determine the presence of cognitive impairment, whereas MMSE scores will be used to confirm the absence of dementia [50].

#### Screening stage 2 (SS2)

SS2 will be performed to determine if cognitive impairment is sufficient to be diagnosed as MCI; SS2 will be performed within 1 week from SS1. A professional team of neurologists and nurses will assess participants’ cognitive function subdomains in detail, including memory, executive function, language, visuospatial abilities, attention, and reaction speed.

#### Diagnostic criteria

MCI diagnosis is based on Petersen criteria are as follows [51]: (1) memory complaint, preferably corroborated by an informant; (2) objective memory impairment for age (MoCA score ≤ 13/14 for illiterate individuals, ≤ 19/20 for individuals with 1 to 6 years of education, or ≤ 24/25 for individuals with 7 or more years of education); (3) essentially intact ADL (ADL score < 25 for age ≥ 75 years and < 23 for age < 75 years) [52]; and (4) not demented (MMSE = 24–30). The final clinical diagnosis will be made by experienced neurologists according to the Diagnostic and Statistical Manual of Mental Disorders, Fifth Edition [53].

#### Inclusion criteria

Eligible participants will meet the following criteria: (1) age ≥ 60 years, (2) diagnosis of MCI, (3) visual and auditory acuity adequate for neuropsychological testing, and (4) able to provide written informed consent and willingness to comply with study visits/testing over the intervention and assessment period.

#### Exclusion criteria

The exclusion criteria of participants are as follows: (1) severe physical dysfunction such as hearing and visual impairment that limits testing or SDTICA program application, (2) history of mental illness or congenital mental retardation, (3) coma, serious disease, or terminal-stage disease, (4) the presence of other neurological diseases that can cause brain dysfunction, (5) intake of any cognitive-impairing/-enhancing medications, and (6) those undergoing other non-pharmacological interventions.

### Sample size determination

The sample size was calculated based on MoCA score improvement reported in our previous study that evaluated the effect of creative expressive therapy on improving cognitive function in patients with MCI [54]. The MoCA scores were 24.68 ± 1.84 (intervention group) and 23.13 ± 1.68 (control group) in our previous study. Using PASS Version 11.0 software (NCSS, Kays-vile, Utah, USA), a sample size of 25 participants per group was determined as being sufficient to detect an effect with a type 1 error rate of 5% (α = 0.05) and 90% power (β = 0.10). To account for clustering, the sample size was calculated according to the requirements of the cluster RCT [55]. Given that interclass correlation coefficient = 0.01 [56], N (individual RCT the required sample size) = 50, “n” means sample size for each cluster, and “k” means number of clusters, the required sample size for each group was calculated. Considering a 15% attrition rate, a total of [(49.5*k)/(0.85*k-0.425)] participants are required.

### Randomisation, blinding, and allocation concealment

Cluster randomisation will be used to ensure blinding and avoid contamination between groups [40]. Randomisation will occur after participant recruitment, informed consent, and complete baseline assessment. A nursing home is referred to as one cluster in this study. We will randomly select eligible nursing homes from all five-star nursing homes in order to minimize the baseline differences in environment, facilities and equipment, operation management, and service provision. A researcher (not involved in participant recruitment and evaluation) will perform the randomisation of nursing homes via lottery. Allocation will be concealed from the assessors.

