### Data analysis

The study will be analysed and reported according to the CONSORT statement for cluster RCTs. The data analyses will be performed using IBM SPSS Statistics Version 21.0 software (IBM, Armonk, New York, USA). Demographic and other baseline characteristics will be summarised using descriptive statistics. Continuous variables with normal distribution will be presented as mean ± standard deviation; non-normal variables will be reported as median (interquartile range). The balance of the baseline data of the intervention and control groups will be compared using the two independent samples t-test, Chi-square test, Fisher’s exact test, and Mann-Whitney U rank-sum test. A mixed-effects model accounting for clustering effects will be used to obtain effect estimates, 95% confidence intervals, and p-values for all outcomes; this will demonstrate whether objectively measured neuropsychological test scores improved in the intervention group compared with the control group at 14 and 36 weeks.

In addition, some potential confounders such as age, sex, and education level will be adjusted. To minimize selection bias, statistical analyses will be based on an intention-to-treat (ITT) approach [74], and missing data will be imputed using the multiple imputation method. As a sensitivity analysis, we will perform per-protocol analyses [75], including only the participants who completed the entire intervention process with compliance greater than 80% and outcome assessment at two time points. A value of *P* < 0.05 will be considered significant and the alpha level will be two-sided. Data management will be the primary responsibility of the research team. All data will be securely stored in an electronic database and accessible only to researchers who meet the research ethics approval.

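### Homes are allocated by plain 1:1 lottery although every home's baseline data are known first; with six or more homes, a constrained draw would balance baseline cognition and education better at little cost

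*Protocol article*

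**What the plan says.** The protocol article, under Randomisation, blinding, and allocation concealment, makes the home the unit ("A nursing home is referred to as one cluster in this study"). It gives the method: a researcher outside recruitment and evaluation "will perform the randomisation of nursing homes via lottery". It also gives the timing: "Randomisation will occur after participant recruitment, informed consent, and complete baseline assessment". The text after Fig. 1, under Study design, setting, and ethics, adds the ratio: "The nursing homes will be randomised on a 1:1 basis". No stratification, pairing, minimisation or constraint is described.

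Two other features bear on balance. Homes are chosen "from all five-star nursing homes in order to minimize the baseline differences in environment, facilities and equipment, operation management, and service provision". Under Data analysis, "A mixed-effects model accounting for clustering effects will be used to obtain effect estimates", and "some potential confounders such as age, sex, and education level will be adjusted". The number of homes, k, stays a symbol in Sample size determination.

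**The concern.** When whole homes are allocated and there are not many of them, a plain draw can leave the arms visibly different at baseline. Many cluster trials must accept this because they randomise before residents are recruited. This trial does not: its order of events puts each home's mean MoCA, education mix and number of participants in hand before the draw. A balanced draw needs exactly that information.

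Education deserves particular attention. The MoCA entry cut-offs under Screening stage 1 run from 13/14 for illiterate residents to 24/25 for those with seven or more years of schooling. Homes with different education mixes can therefore be expected to start at different MoCA levels. A visible gap in baseline cognition would widen the uncertainty of the primary comparison and leave it open to challenge. The planned baseline comparison tests can show such a gap only after allocation, when the draw can no longer be changed.

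**Working it through.** **Inputs from Sample size determination.** SDs 1.84 and 1.68, MoCA difference 24.68 − 23.13 = 1.55, ICC 0.01, attrition 15%, total = 49.5k/(0.85k − 0.425). From Intervention: 8–10 people per group.

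**1. The plan's total.** The cluster step solves n·k = 50 × [1 + (n − 1) × 0.01], giving n = 49.5/(k − 0.5) per home. Dividing by 0.85 and multiplying by k reproduces the printed formula.

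| k | Recruited total | Per home |
|---|---|---|
| 4 | 66.6 | 16.6 |
| 6 | 63.5 | 10.6 |
| 8 | 62.1 | 7.8 |
| 10 | 61.3 | 6.1 |

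One group of 8–10 per home points to about 6–8 homes. This is an inference: the formula accepts any k, and about 17 per home (two groups) would fit k = 4.

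**2. Baseline gap under the lottery.** Pooled SD = √[(1.84² + 1.68²)/2] = 1.762. For equal-sized homes and a recruited total N with m per home, the arm difference in mean baseline MoCA has SD = 1.762 × √{4 × [1 + (m − 1) × ICC]/N}.

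- k = 6: 1.762 × √(4 × 1.096/63.5) = 0.46. P(|gap| > 0.5) = P(|Z| > 1.08) = 28%.
- k = 8: 1.762 × √(4 × 1.068/62.1) = 0.46, again 28%.

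The threshold of 0.5 points is my choice; it is 0.5/1.55 = 32% of the planned effect. Recruited numbers are used because baseline is measured on everyone recruited.

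**3. How much is due to clustering.** Individual randomisation of the same 63.5 people gives SD = 1.762 × √(4/63.5) = 0.44 and a probability of 26%. At the plan's ICC, clustering adds about two percentage points. The rest is ordinary variation between residents.

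**4. Constrained draw.** I simulated three independent home-level covariates (20,000 sets), scored every 1:1 allocation by the sum of squared arm differences, kept the better half, and drew one at random.

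| k | Allocations kept | SD of MoCA gap | P(gap > 0.5): lottery | P(gap > 0.5): constrained |
|---|---|---|---|---|
| 6 | 10 of 20 | 0.46 → 0.32 | 28% | 11.6% |
| 8 | 36 of 70 | 0.46 → 0.32 | 28% | 11.2% |

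**5. Sensitivity to ICC.** At an assumed ICC of 0.05, which is not in the protocol, the lottery figures become 35% (k = 6) and 33% (k = 8), and the constrained figures 19% and 17%.

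**6. Cost of repairing home-level imbalance afterwards.** Between-home degrees of freedom are k − 2. At k = 6, one home-level covariate takes them from 4 to 3 and the two-sided 5% critical t from 2.78 to 3.18.

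**The case against.** The strongest reply is that nothing here is an error. A 1:1 draw by someone outside recruitment and evaluation, made after baseline, is proper randomisation, and choosing a constrained draw is a design preference. That stands. A reader might infer that the lottery biases the comparison or leaves imbalance uncontrolled; the protocol supports neither. Chance imbalance does not bias a randomised comparison. Five-star restriction aims at home-level differences, residents enter through education-specific MoCA limits and an MMSE range, and the adjustment list opens with *such as*, so baseline MoCA is not excluded. None of these, however, balances residents' cognition, education mix or numbers across arms.

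A reader might also infer that the homes are known to be few. They are not: k is never given, and the formula still yields 59.7 residents at k = 20. Nor does the ratio allow unequal arms of the kind that independent coin tosses produce, since allocation is stated as 1:1.

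Purely home-level factors also matter less than they may seem. At ICC 0.01 the between-home SD of the outcome is √0.01 × 1.762 = 0.18 points, or 11% of 1.55. A gap of one between-home SD in a home-level factor therefore has limited leverage on the result. The case for a constrained draw rests mainly on resident-level baseline cognition and education, which covariate adjustment also addresses in part.

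**Conclusion.** The point holds as a recommendation for improvement, not as a flaw in validity. The plan gathers what a balanced draw needs and then does not use it. With 6–8 homes at ICC 0.01, the chance of a baseline MoCA gap above 0.5 points falls from about 28% to about 11 to 12%, with no extra residents, visits or data. The benefit is precision and credibility.

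This rests on several assumptions:
- k is 6–8, inferred from group size and the total.
- The earlier study's SD of 1.76 applies at baseline; a wide education mix could make the true SD larger.
- Homes are of equal size.
- The three balancing variables are independent.

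With fewer than six homes the recommendation lapses: k = 4 has only six possible 1:1 allocations, so a constraint leaves too little randomness.

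**What to change.** State the number of homes once recruitment closes. If at least six join:

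- List all 1:1 allocations. Score each on home-mean baseline MoCA, education mix and number of participants, and keep the better-balanced half. Let the same independent researcher draw one by computer with a stored seed.
- Prespecify resident-level baseline MoCA and education in the mixed model, so that the analysis reflects the balancing.
- Do not add number of participants to the model. It is constant within a home and would use one of the k − 2 between-home degrees of freedom. Balance on it in the draw only.

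If fewer than six join, keep simple randomisation and say so.

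The cost is a short script run once and two prespecified covariates, one of which (education) is already named. The draw also comes from a limited set: 10 of 20 allocations at k = 6, which is still random.
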